**Fig. 2 Fig2:**
[figure not shown]
Accelerated dose escalation and switching to standard 3+3 dose escalation scheme.

### Participants

#### Major inclusion criteria

Females aged ≥ 19 yearsHistologically confirmed epithelial ovarian cancer, fallopian tube cancer, or primary peritoneal cancer regardless of initial stage at diagnosisPlatinum-refractory (disease progression during platinum-based chemotherapy) or platinum-resistance cancer (disease progression within 24 weeks from completion of platinum-based chemotherapy) in which patients progressed after second-line or more platinum-containing chemotherapy will be includedA life expectancy ≥ 12 weeks assessed by investigators comprehensively judging clinical statusA prior number of cytotoxic chemotherapy lines ≤ 5Eastern Cooperative Oncology Group (ECOG) performance status ≤ 1

#### Major Exclusion Criteria

Platinum-sensitive ovarian cancer (disease progression after 24 weeks from completion of platinum-based chemotherapy)Prior number of cytotoxic chemotherapy lines > 5Known or suspected hypersensitivity or intolerance to the active ingredient or excipients of PHI-101Patients with severe cardiovascular disease, intake or absorption disability (dysphagia, intestinal paralysis or obstruction, and history of gastrointestinal surgery significantly affect absorption), autoimmune or inflammatory disease, severe respiratory disease, active hepatitis B or C, and several infectious diseases will be excluded.ECOG performance status ≥ 2

### Primary Endpoints

#### Primary objectives

The primary objective of this study is to assess DLT and MTD of PHI-101. In addition, the presented by the cohort and MTD will be determined. The definition of DLT is presented in Table 1.

#### Secondary objectives

Secondary objectives include assessing the IP tolerability by dose interruption, dose reduction, and dose termination due to adverse events. In addition, IP safety will be assessed by treatment-emergent adverse events, adverse drug reactions, serious adverse events, serious adverse drug reactions, and adverse events leading to withdrawal. Adverse events are defined as any unfavourable and unintended sign, symptom, or disease during the study period. Adverse events will be assessed according to the Common Terminology Criteria for Adverse Events (CTCAE) version 5.0 criteria. Also, physical examination, laboratory tests, vital signs, electrocardiogram will be performed for safety evaluation, and the investigators, including physicians and coordinating research nurse, will assess the adverse events for every visit.

Pharmacokinetic assessment will be done on cycle 1 day 1 (pre-dose, 0.5-, 1-, 2-, 4-, 6-, 8- and 24-hours post-dose), day 8 (pre-dose), day 15 (pre-dose, 0.5-, 1-, 2-, 4-, 6-, 8- and 24 hours post-dose), day 22 (pre-dose), cycle 2 day 1 (pre-dose and 2-4 hours post-dose), cycle 2 day 1 (pre-dose and 1-3 hours post-dose), and then every three cycles on day 1 to end of treatment (EOT). For pharmacokinetic analysis of PHI-101, 6mL of blood will be collected using a K2 EDTA tube and then centrifuged at 2,000g at 4°C for 10 minutes. The separated supernatant (plasma) will be dispensed into two tubes by 1mL or more and stored in a freezer at -70°C or lower.

Genetic variation, including HRD related genes including BRCA mutation based on tumour next-generation sequencing test results, will be collected for exploratory assessment. Additional biopsy or sequencing is not mandatory for the participants, but previously performed analysis results based on medical records will be analysed. For the efficacy assessment, a radiologic tumour response assessment will be done based on RECIST version 1.1.

The participants will be required to write a drug diary to improve adherence. Adequate and optimal supportive care will be permitted during the study, and therapies that may affect the efficacy and safety assessment of IP will be prohibited.

### Sample size

Given the characteristics of a phase I study, calculating the sample size based on a statistical hypothesis was not conducted in this study. Instead, the target number of subjects will be determined to ensure the smallest possible number of subjects participating in the study. A total of six cohorts are planned in the study, and a minimum of one to a maximum of six subjects will be enrolled in each cohort (Table 2). Therefore, approximately we expect six to 36 patients to be enrolled.

**Table 2 Tab2:** Dose cohort and escalation increment

Dose level (cohort)	Daily dose of PHI-101 (once daily)		Escalation increment from the previous dose	
-1	20 mg	1 tab.	- 20 mg	- 50%
1 (starting dose)	40 mg	2 tab.	-	-
2	80 mg	4 tab.	40 mg	100%
3	120 mg	6 tab.	40 mg	50%
4	160 mg	8 tab.	40 mg	33%
5	200 mg	10 tab.	40 mg	25%
6 (maximum planned dose)	240 mg	12 tab.	40 mg	20%

### Statistical method

Safety analysis will be done on the subjects who received at least a single dose of the IP, and the number of events will be presented using the number of events by cohort. In addition, the DLT assessment will be done on the subjects who received at least a single dose of the IP and had DLT assessments during cycle 1. PK parameters including C_max_, C_max,ss_, C_min,ss_, C_av,ss_, AUC_t_, AUC_τ_, AUC_inf_, T_max_, T_max,ss_, t_1/2_, peak-trough fluctuation (PTF), accumulation ratio (AR), CL/F, CL_ss_/F, and V_z_/F will be calculated.

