## Methods/Design

### Trial design

Chk2 inhibitor for Recurrent EpitheliAl periToneal, fallopIan, or oVarian cancEr (CREATIVE) trial is a prospective, multi-centre, phase I dose-escalation study to determine the dose-limiting toxicity (DLT) and maximum tolerated dose (MTD) of PHI-101. This study was approved by each institutional review board of all participating institutions and funded by Pharos iBio Co., Ltd. (Gyeonggi-do, Republic of Korea). Four participating institutions are listed: Ajou University Hospital, Bundang Seoul National University Hospital, Seoul National University Hospital, and Seoul ST. Mary's Hospital.

The investigators will obtain the informed consent form from all participants before any screening examinations. As shown in Figure 1, study participants will be orally administered PHI-101 (2 to 12 tablets/day) at a predetermined dose cohort once daily each for one cycle (28 days), and DLT will be observed during the first cycle of each subject by the list depicted in Table 1. Participants will continue to take PHI-101 until the following termination criteria are met: radiologic progression or clinical progression; death; withdrawal of consent; unacceptable adverse event; dose interruption longer than four weeks. Dose adjustment is not allowed during the DLT observation period (cycle 1, 28 days). Although treatment-specific side effects are not known so far, we included possible side effects shown in preclinical study results depicted in Supplementary Table 2 to the DLT list. During the study period, concomitant medication to control symptoms other than tumours is permitted. However, any antineoplastic therapies other than the IP (surgery, radio(chemo)therapy, cytotoxic chemotherapy, targeted therapy, and immuno-oncologic drug) and alternative treatments (nonprescription drug, herb, or homoeopathy) will be prohibited.

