**Other toxicity**	
ADR with dose interruption (temporary discontinuation) of PHI-101 for > 4 weeks	

Abbreviations: ALP, alkaline phosphatase; ALT, alanine transferase; AST, aspartate transferase; CTCAE, Common Terminology Criteria for Adverse Events; ECG, electrocardiography; GGT, γ-glutamyl transferase; ULN, upper normal limit; WBC, white blood count.

The study scheme for the cohort assignment is described in Fig. 2 [11]. The accelerated dose escalation scheme, which assesses DLT in a single subject in each cohort, will be applied for this phase I study. This accelerated dose-escalation scheme will be sustained until adverse drug reaction related to investigational product (IP) same or greater than grade 2 occurs. If IP-related toxicity ≥ grade 2 does not occur, DLT can be assessed at the higher dose cohort according to the recommendation of the safety review committee (SRC). If IP-related toxicity ≥ grade 2 occurs, additional two subjects will be enrolled in the same dose cohort, and the study will be switched to the standard 3+3 scheme. If DLT is observed in > 1 out of 6 subjects in a specific cohort (χ) and DLT is observed in ≤ 1 out of 6 subjects in the cohort (χ-1) that is one level lower than the specific cohort, the one level lower cohort (χ-1) will be considered as MTD. The dose of PHI-101 will be escalated until MTD is determined, and if the MTD is not determined at the maximum planned dose, dose-escalation will be ended at that dose.

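### Raw event counts by cohort, the only safety summary the article names, do not by themselves show how adverse-event risk changes with dose

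*Protocol article*

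**What the plan says.** The Statistical method section sets the safety population: "Safety analysis will be done on the subjects who received at least a single dose of the IP". In the same sentence it names the summary: "the number of events will be presented using the number of events by cohort". The article gives no subject-level incidence, proportion or exposure measure for safety.

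Three features of the design bear on that choice.

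- **Cohort size.** Under Sample size, "a minimum of one to a maximum of six subjects will be enrolled in each cohort". Size depends on what is observed. Under Trial design (the paragraph after Table 1), a dose level is tested in a single subject unless an IP-related reaction of grade 2 or more occurs. In that case "additional two subjects will be enrolled in the same dose cohort, and the study will be switched to the standard 3+3 scheme".
- **Duration.** Under Trial design, "Participants will continue to take PHI-101 until the following termination criteria are met". Those criteria are progression, death, withdrawal of consent, an unacceptable adverse event or an interruption of more than four weeks. No number of cycles is fixed.
- **Dose received.** Trial design rules out dose adjustment in the 28-day DLT window. Secondary objectives lists dose reduction among the tolerability measures, so a subject may later be on a dose other than that of the cohort.

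**The concern.** A count of events rises with the number of people treated and with the time each is treated, and one subject with a recurring event can supply much of it. Here the first two vary between cohorts by design. Cohort size is also linked to toxicity: a reaction of grade 2 or more brings further subjects into the cohort, so the count goes up once through the reaction and again through the subjects it adds.

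A table of event counts by dose level invites the reader to look down the column for a dose trend. As specified, part of any trend would reflect enrolment and follow-up rather than the drug. Toxicity after the first 28 days lies outside the DLT window and appears only in these safety summaries.

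**Working it through.** **Inputs.** Six planned cohorts and one to six subjects per cohort (Sample size). Open-ended treatment in 28-day cycles (Trial design). The article gives no event rate or mean duration, so the values used below for these are assumptions.

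**Step 1: reproduce the plan's own figure.** Sample size states that "approximately we expect six to 36 patients to be enrolled". The smallest total is 6 cohorts × 1 = 6 and the largest is 6 × 6 = 36. The figure reproduces, which confirms that one to six per cohort is the intended range.

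**Step 2: effect of cohort size alone.** Expected events = subjects × mean cycles × events per subject-cycle. With the same rate and the same mean cycles at every dose, those two factors cancel. The ratio of counts is then the ratio of cohort sizes: 6 / 1 = 6, or 3 / 1 = 3 for a single-subject cohort against one of three. This needs no assumed rate, but it does assume that rate and exposure are equal.

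**Step 3: add unequal exposure (assumed).** Take 1 event per subject-cycle at both doses.

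- 1 subject × 1 cycle × 1 = 1 event
- 6 subjects × 4 cycles × 1 = 24 events

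That is a 24-fold difference with no dose effect.

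**Step 4: the direction can reverse (assumed).** Let the true rate double from the lower to the higher dose.

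- Lower dose: 6 subjects × 4 cycles × 0.5 = 12 events
- Higher dose: 3 subjects × 2 cycles × 1.0 = 6 events

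The rate doubles and the count halves. Dividing by subject-cycles recovers the truth: 12 / 24 = 0.5 and 6 / 6 = 1.0.

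**Step 5: subjects affected.** Six events in a cohort of six may be one subject with six events or six subjects with one each. The count is 6 both times. The incidence is 1/6 in the first case (exact 95% interval 0.4% to 64.1%) and 6/6 in the second (54.1% to 100%). Knowing the cohort size does not separate the two.

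**Step 6: what denominators can and cannot do.** Exact 95% intervals are 0% to 97.5% for 0/1, 0% to 70.8% for 0/3 and 0.4% to 64.1% for 1/6. Proportions remove the distortion from cohort size, but they do not make cohorts this small precise.

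**The case against.** The strongest reply is that this is a condensed article, and that subject incidence, grade tables and exposure are commonly set out in the full protocol or SAP, which are not shown. The sentence is also loosely worded and does not say that counts will be the sole summary. Had the article been silent, there would be no point to raise. It is not silent: it names a measure, and that measure suits the design poorly. What stands of the reply is that the full documents may already contain the better summary, in which case only the article's sentence needs to change.

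A second reply is that cohort sizes will be known, so a reader can set counts against n. That answers the six-fold effect in Step 2. It does not answer exposure, repeat events or the number of subjects affected. For this reason it would be too strong to say that the tables cannot show a dose relation. They do not show it by themselves.

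A third reply is that a single-subject cohort is itself a sign of low toxicity under the escalation rule, and that single-subject cohorts need not occur at all, since a grade 2 reaction at the first level starts the 3+3 scheme at once. This is right. Lower doses are therefore not bound to look safer.

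A reader might also infer two things that the article does not support.

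- **That tolerability is to be shown as event counts too.** The sentence covers the safety analysis. Secondary objectives treats "assessing the IP tolerability by dose interruption, dose reduction, and dose termination due to adverse events" separately from safety, and no summary measure is stated for those items.
- **That the event tables drive the recommended phase II dose.** The Discussion part of the abstract ties that dose to DLT and MTD. DLT is judged per subject in a fixed 28-day window, and the MTD rule has an explicit denominator of six, so neither is open to this distortion.

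**Conclusion.** The point holds for the secondary descriptive safety tables. The one summary named there mixes dose with cohort size, exposure and recurrence within a subject.

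The size that rests on the document is up to six-fold between cohorts at equal rate and exposure, which is the cohort-size range carried through to the counts. The 24-fold difference and the reversal rest on assumed rates and durations. They show what is possible and do not predict what this trial will see.

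Determination of DLT and MTD and the enrolment of six to 36 are unaffected. The change is worth making because the better summary needs no new subjects or visits, but it does not put the trial's primary conclusion in doubt.

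**What to change.** Reword the safety sentence under Statistical method so that the main summary, by cohort, is the number and proportion of treated subjects with at least one event, by worst CTCAE grade. Show cohort size and subject-cycles of exposure in the same table. Keep event counts as a secondary summary. For events after cycle 1, flag the dose being taken at onset, so that an event on a changed dose is not read as an event at the cohort dose.

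If the full protocol or SAP already specifies this, bring the article's sentence into line with it.

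The cost is wording and slightly more table work. Graded events are already recorded, and the drug diary and e-CRF should supply the exposure and dose at onset. The limit is precision: with one to six subjects per cohort the proportions stay imprecise and should be read as description.

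### The DLT analysis set asks for one dose and DLT assessments in cycle 1, not a completed 28-day window, so early leavers without a DLT can stay in the denominator

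*Protocol article*

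**What the plan says.** **Analysis set.** The Statistical method section carries out the DLT assessment on "subjects who received at least a single dose of the IP and had DLT assessments during cycle 1".

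**Window.** Trial design states that "DLT will be observed during the first cycle of each subject by the list depicted in Table 1", and puts the DLT observation period at cycle 1, 28 days, with once-daily dosing.

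**Reasons for stopping.** The same section lists "radiologic progression or clinical progression; death; withdrawal of consent; unacceptable adverse event; dose interruption longer than four weeks". All but the last can fall inside cycle 1.

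**Use of DLT data.** Trial design (text after Table 1) says: "The accelerated dose escalation scheme, which assesses DLT in a single subject in each cohort, will be applied for this phase I study". As long as no IP-related toxicity of grade 2 or higher is seen, the next dose level may be opened if the safety review committee (SRC) recommends it. Two more subjects are added, and the trial moves to 3+3, when such toxicity occurs. The MTD is the level with at most 1 DLT in 6 subjects, lying just below a level with more than 1 in 6.

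**Enrolment.** The Sample size section plans six cohorts of one to six subjects, 6 to 36 in all.

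**The concern.** The stated set and the stated window do not match. One of 28 planned doses, plus DLT assessments within the cycle, satisfies the definition. A subject who stops in the second week because of progression, withdrawn consent or missed doses therefore belongs to the set. With no DLT recorded, she adds to the denominator and not to the numerator.

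Table 1 sharpens the problem. Nine of its rows contain a criterion that needs more than 7 days' duration: neutrophil count, nausea, tumour pain, grade 3 vomiting, fatigue, anorexia, asymptomatic liver enzymes, and the two rows for liver metastases. A subject observed for 7 days or less cannot meet any of these.

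DLT and MTD are the primary endpoint, and few subjects determine them. If partly observed subjects count as full observations, the error runs in one direction: a lower apparent DLT rate, a higher MTD, and later subjects treated at a higher dose on thinner evidence than the design intends.

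**Working it through.** **Plan's own figure.** 6 cohorts × 1 = 6 and 6 × 6 = 36, which reproduces the stated 6 to 36. No hypothesis-based sample size is given, so there is no power figure to check.

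**Inputs from the article.** A 28-day window; one subject per cohort in the accelerated stage; the rule of at most 1 in 6.

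**Assumptions (not in the article).** True 28-day DLT probability p = 0.33 or 0.50; time to DLT uniform over 28 days; a leaver exits after day 8. The article names the standard 3+3 scheme but its figure is not shown. I take the usual rule: escalate on 0 of 3, or on 1 of 3 followed by 0 of 3.

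**1. DLT probability that can be seen in a leaver,** p × 8/28
- p = 0.33: 0.33 × 8/28 = 0.094
- p = 0.50: 0.50 × 8/28 = 0.143

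**2. 3+3 escalation,** P(0 of first 3) + P(1 of first 3) × P(0 of next 3)

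| | p = 0.33 | p = 0.50 |
|---|---|---|
| All fully observed | 0.301 + 0.444 × 0.301 = 0.434 | 0.125 + 0.375 × 0.125 = 0.172 |
| One leaver among the first three | 0.407 + 0.443 × 0.301 = 0.540 | 0.214 + 0.464 × 0.125 = 0.272 |

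With a constant daily hazard and exit on day 7 instead, the one-leaver figures are 0.539 and 0.268. The result hardly depends on the timing model.

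**3. Without conditioning on a leaver.** If a share L of all subjects leaves after day 8, the effective probability is (1 − L) × p + L × p × 8/28. For p = 0.33:
- L = 10%: 0.9 × 0.33 + 0.1 × 0.094 = 0.306; escalation 0.334 + 0.442 × 0.334 = 0.48
- L = 30%: 0.7 × 0.33 + 0.3 × 0.094 = 0.259; escalation 0.406 + 0.427 × 0.406 = 0.58

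For p = 0.50 and L = 10%: 0.9 × 0.50 + 0.1 × 0.143 = 0.464; escalation 0.154 + 0.400 × 0.154 = 0.22, against 0.17.

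**4. The stated rule of at most 1 in 6,** P(0 of 6) + P(1 of 6), taking six subjects as enrolled
- p = 0.33: 0.090 + 0.267 = 0.358 with full observation; 0.122 + 0.314 = 0.436 with one leaver
- p = 0.50: 0.016 + 0.094 = 0.109; with one leaver 0.027 + 0.138 = 0.165

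**5. Accelerated stage.** The gate here is IP-related toxicity of grade 2 or higher, not DLT. Let q be its 28-day probability, again with uniform timing. The chance that a lone subject shows none is 1 − q with full observation and 1 − q × 8/28 with exit after day 8.
- q = 0.33: 0.67 and 0.906
- q = 0.50: 0.50 and 0.857

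With 10% leavers and q = 0.33, the unconditional figure is 0.9 × 0.67 + 0.1 × 0.906 = 0.69. These are chances that the trigger is not seen; the SRC decision still follows.

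**The case against.** The strongest reply is that this is a condensed article. Evaluability and replacement rules usually sit in the full protocol, which is not shown, so their absence alone is no fault. That is right, and the point does not rest on it. It rests on a definition that the article states and that does not fit its own window.

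A second reply is that having DLT assessments during cycle 1 may mean having all of them. That reading is possible, but the sentence does not say so, and it would still set no minimum exposure.

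A reader might go further than the text allows in four ways:
- **That the plan declares an early leaver DLT-free and lets her clear a dose level by herself.** No sentence says so. The first part follows from the set's definition. The second is only a possibility, because escalation is permissive and needs an SRC recommendation. The article does not, however, state any minimum follow-up for that recommendation.
- **That the set drives every escalation decision.** The accelerated stage turns on toxicity of grade 2 or higher.
- **That unexposed subjects are counted.** At least one dose is required.
- **That exits for toxicity are lost.** A DLT before exit is counted, and in the accelerated stage IP-related toxicity of grade 2 or higher adds two subjects. The gap concerns exits for other reasons, before such toxicity appears.

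The article gives no figure for how often subjects leave before day 28. Entry requires a life expectancy of at least 12 weeks and ECOG status of 1 or lower, and a drug diary supports adherence. On the other side, the disease is platinum-refractory or platinum-resistant with up to five prior lines, so some early exits are plausible.

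**Conclusion.** The point holds in this limited form: the stated DLT set admits subjects who were observed and dosed for only part of the 28-day window. Followed literally, it biases the DLT rate down and the MTD up.

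The size depends on how many subjects leave early. Given one leaver among the first three, the chance of escalating rises by about 0.10 (0.43 to 0.54 at a 33% DLT rate, 0.17 to 0.27 at 50%). Averaged over a trial in which 10% leave after day 8, the rise is about 0.05 (to 0.48 and 0.22). The DLT rates, uniform timing, exit day, leaver shares and usual 3+3 rule are all assumptions.

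The wording should be settled before escalation decisions rest on it. If the full protocol already has a stricter rule, the published sentence misstates it and should be aligned.

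**What to change.** Replace the sentence in Statistical method with a definition along these lines: DLT-evaluable subjects are those who had a DLT in cycle 1, or who completed the 28-day window with the scheduled DLT assessments and at least a minimum exposure that the sponsor states in advance. Then:

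- base both the single-subject cohorts and the 1-in-6 MTD rule on this set;
- replace non-evaluable subjects in the same cohort and keep them in the safety set;
- restate the Sample size section so that one to six per cohort and 6 to 36 overall refer to evaluable subjects. Otherwise replacement could breach the stated maxima.

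The cost is a short change of wording in two sections, a few replacement subjects, and possibly one more cycle for a cohort. Total enrolment may then exceed 36.
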